### 2.4. Data Collection Procedure, Monitoring, and Management

Once participants have been informed and agree to participate in the study, data will be collected for statistical analysis. This data collection will take place in the period February–June 2021. Initial assessment (Pre) and final 8-week assessment (Post) will be carried out by the research team with the cardiology, rehabilitation, and physiotherapy departments. The data will be aggregated to a research database created for this purpose and managed by the principal’s research using exportable data tables for statistical analysis. 

The research is designed in 4 stages, as presented in Figure 1 in a study design flow diagram:

Stage 1 includes 2 different processes: firstly the identification of candidates, the provision of prior information and the signing of informed consent in the event that the subjects agree to participate. Secondly, the assessments by the cardiology department with ergometry and biochemistry test at (T0-Pre). This stage ends with the referral to the rehabilitation department.

Stage 2 includes: the assessments by the rehabilitation department with quality of life, functional capacity outcomes, and comorbidity index added to previous clinical information. At this stage, the Modified Borg Scale Education is offered to participants to assess their level of fatigue during exercise. A personalized CTR program is proposed according to the Physiotherapy Department. This stage ends with the referral to the Physiotherapy department and CTR staff.

Stage 3 includes: 8 weeks CTR program with the supervision of the Physiotherapy Department and the CTR staff. An initial 1-to-1 session is offered with technology management and patient education. Daily follow up sessions include the progression, barriers of use, and adverse event records. CTR team will updates programs according to participant’s feedback and rehabilitation supervision.

Stage 4 includes: Final assessments and evaluation (T1-Post). At this stage, cardiology, rehabilitation, physiotherapy and principal research are compiled into the results of clinical and self-reported outcomes after 8 weeks CTR program including: biochemistry, ergometry, quality of life, and functional capacity. At this stage, satisfaction and usefulness, economic data safety, and adherence records will be added to research data’s for statistical analysis

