### 2.1. Patients

The trial includes adults with a diagnosis of low-risk CVD with class I heart failure according to the NYHA (New York Heart Association) functional assessment criteria (24), diagnosed by the Cardiology and Rehabilitation team of the Hospital of Melilla. Patients must live in Melilla during the intervention phase, have mobile technology with an internet connection at home (including one of the following devices: desktop personal computer, laptop, tablet, or smartphone), and be able to access email or instant messaging frequently and reliably. Patients who suffered non-mild cardiac events prior to the first contact with this research, those whose pathologies are not classified as CVD, and those subjects who are not in full cognitive capacity that allows them to use new technology tools will be excluded. Patients will be excluded if they have any absolute or relative contraindications to exercise testing as per the American Heart Association guidelines [20]. Inclusion and exclusion criteria is show in Table 1.

In order to generate sufficient data for the development of this research, a sample size of (*n* = 30) patients will be recruited. The primary aims of this sample size determination is to evaluate whether the proposed intervention is feasible, safe, and effective. A larger randomized controlled trial that would have adequate power could be designed based on what was learned in this study. The strategies to achieve an adequate inclusion of participants that reach the target sample size include the multidisciplinary collaboration of the team from the Regional Hospital of Melilla (Cardiology Department, Head of the Rehabilitation Service and the Physiotherapy team). The collaborators were informed about the characteristics of the study in personal interviews and presentation. We ensured that the recruitment of patients has a socio-demographic diversity in relation to their social origin, gender, ethnicity, and education adapted to the particularities of the reference population. For the development of this research, an intentional non-probabilistic type of sampling will be used for the convenience of the study, due to the characteristics of the subjects. This trial has the approval of the Andalucía Ethics Committee with HIP version 17112020.

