
#### 2.3.2. Secondary Explanatory Variable

Satisfaction and usefulness: The acceptance and usefulness of telemedicine applications is a prerequisite for identifying the potential clinical benefits of this technology. It is therefore important to complement this research with tools that examine patient satisfaction and perception [29]. An adaptation of the Telemedicine Satisfaction and Usefulness Questionnaire (TSUQ), whose psychometric analysis supports construct validity and internal consistency reliability, and which is available in English and Spanish, will be used [29]. The instrument used showed high reliability (Cronbach’s alpha 0.8) and evidence of validity with respect to perception in telemedicine [30]. It includes 17 questions that are assessed with a 5-point Likert subjective scale (1 totally disagree and 5 completely agree). The individual obtains scores from 17 to 85. The higher the score, the better the perception of the telerehabilitation intervention. Therefore each of the scores of the 17 variables indicated and finally the total score of the Test will be analyzed [29,30].

Analysis of the cost-effectiveness: To assess the cost-effectiveness of the telerehabilitation intervention, the international guidelines for conducting cost analyses in randomized clinical trials will be followed [31]. Such an economic analysis is based on the health sector perspective, which means that only costs corresponding to health interventions will be considered, and not related costs to the patient. Therefore, only costs related to the provision of health services will be taken into account [32].

Costs are divided into two categories of variables: firstly, costs related to clinical aspects (direct costs) and secondly, costs related to the use of the technology (indirect costs).

Direct costs: Numerical variable calculated on the basis of the number of hours of intervention and the cost of the physiotherapist according to the hourly wage in the health system in the centers where the research is carried out. It will be calculated based on the recording of the number of sessions in both groups.

Indirect costs: Numerical variable calculated based on the cost of using the technology for the telerehabilitation platform.

Adherence and safety: Participants will be advised to report and record barriers of use and any adverse event during the study. Number of sessions are automatically registered by the CTR tool.

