### 2.5. Statistical Analysis

This research is a single center prospective controlled trial pre/post design. The results of the trial research will be presented as a summary of the outcome measures, together with the estimated effect size and precision. Statistical analysis will be performed according to the intention-to-treat principle. Patient characteristics will be summarized using frequencies and percentages for categorical factors, and using means and standard deviations for continuous measures in order to have as much information as possible available for exploration and analysis. The effect sizes will be calculated using Cohen’s d, so that the results can be compared to other studies. The outcome measures will be compared before and after the completion of the 8-week CTR program. All statistical analyses will be conducted using SPSS software. Statistical significance was set at *p* < 0.05.

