## 4. Discussion

Telemedicine has the promise of improving quality, increasing patient access, and reducing health care costs [34], and recent advances in telecommunications technologies have boosted the possibility of carrying out rehabilitation processes over the internet [35]. Studies have shown that telerehabilitation is effective in improving clinical outcomes in various pathologies, suggesting that increasing the intensity provided by telerehabilitation is a promising option to be offered to patients (32). This research should provide knowledge about the possibility of implementing CTR programs in the hospital environment, identifying the health resources and costs allocated to define new intervention policies in this group of patients. Unlike other studies that require software implementations in specific devices, our intervention generates few obstacles since it is available in any device that allows internet connection and that patients usually have (PC, laptop, tablet, smartphone), allowing access from any location and different devices prioritizing the use of mobile health. This contrasts with other studies that require a highly complex technological platform, software installation, and multidirectional cameras for controlled clinical control connecting the healthcare provider and the patient [36].

Technical problems (disconnection, device failures) and technological difficulties may arise in connection with the use of technology. However, staff members are available to provide technical support by phone or email, without the need to visit the patient at home to install or check any hardware. As possible adverse events, we considered the lack of improvement and positive evolution of the patient as well as the appearance of a low level of adherence. We also considered as an adverse event the performance of exercise with excessive workload. Patients will be informed of the importance of warning the health professional of any incident or setback in their recovery and their right to withdraw from participation in the research at any time.

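### The TSUQ is scheduled only at the 8-week assessment, with no score planned for patients who leave the research earlier, so the satisfaction part of the feasibility conclusion is at risk of survivor bias

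*Protocol article*

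**What the plan says.** Section 2.4 sets two assessment times: "Initial assessment (Pre) and final 8-week assessment (Post) will be carried out by the research team". Satisfaction appears in the fourth of its four stages, which opens "Stage 4 includes: Final assessments and evaluation (T1-Post" and closes with "At this stage, satisfaction and usefulness, economic data safety, and adherence records will be added to research data’s for statistical analysis". The daily records listed for Stage 3, while the program runs, cover progress, barriers and adverse events, but not satisfaction.

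Section 2.3.2 describes the TSUQ as 17 items scored 1 to 5, with a total from 17 to 85, and says "The higher the score, the better the perception of the telerehabilitation intervention". In Table 2 it is the only measure on the row for feasibility, satisfaction and usefulness. Section 3 lists three things that together will show feasibility: successful delivery, no significant adverse effects, and user satisfaction. It sets no threshold for satisfaction.

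On patients who leave, section 4 says only that they are told of "their right to withdraw from participation in the research at any time". Section 2.5 adds: "Statistical analysis will be performed according to the intention-to-treat principle". The sample size in section 2.1 is stated as "a sample size of (*n* = 30) patients will be recruited", with no dropout allowance.

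**The concern.** Satisfaction is the outcome most exposed to early leaving. A patient who finds the application hard to use, or daily sessions for 8 weeks unacceptable, has a reason both to leave and to give a low score. If the score is obtained only from those present at week 8, the mean describes people who tolerated the program, and it can rise as dissatisfied users depart.

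The other self-reported outcomes have a T0 value that an analysis could use for a patient lost later. The TSUQ can have none, because a patient cannot rate the program before using it. For this outcome the remedy lies in data collection. A later analysis plan can describe how to treat a missing score but cannot recover a questionnaire that was never sent.

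At stake is one of the three supports of the feasibility statement, in a study that section 3 says will determine whether a larger-scale intervention is feasible.

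**Working it through.** **Inputs from the documents.** N = 30 (section 2.1). TSUQ range 17 to 85, a width of 85 − 17 = 68 points (section 2.3.2). TSUQ named once, at Stage 4 (section 2.4). The article gives no dropout rate, expected TSUQ mean or standard deviation, so it has no figure of its own on this point to reproduce.

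**Assumed inputs, for illustration only.** 3, 6 or 9 of 30 scores missing (10%, 20%, 30%); a responder mean of 70; leavers scoring 10 to 30 points below stayers.

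**Step 1: what is scheduled.** The closing sentence of Stage 4 groups satisfaction with adherence and safety records. Those two have a named earlier source: sessions are counted automatically by the application, and adverse events are recorded during the program. The TSUQ has none, so a schedule followed as written yields no score for someone who has left the research before week 8.

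**Step 2: how far the all-starter mean is undetermined.** With k of 30 scores missing, each could lie anywhere from 17 to 85. The width of the undetermined range is 68 × k/30, whatever the responders score:

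- k = 3: 68 × 0.1 = 6.8 points
- k = 6: 68 × 0.2 = 13.6 points
- k = 9: 68 × 0.3 = 20.4 points

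**Step 3: bounds for an assumed responder mean of 70.** Lower bound = (1 − k/30) × 70 + (k/30) × 17; the upper bound uses 85 in place of 17.

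| Missing | Lower bound | Upper bound |
|---|---|---|
| 3 of 30 | 63 + 1.7 = 64.7 | 63 + 8.5 = 71.5 |
| 6 of 30 | 56 + 3.4 = 59.4 | 56 + 17.0 = 73.0 |
| 9 of 30 | 49 + 5.1 = 54.1 | 49 + 25.5 = 74.5 |

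**Step 4: overstatement for an assumed gap.** Overstatement = (k/30) × (mean of stayers − mean of leavers). For gaps of 10 to 30 points this gives:

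- k = 3: 1.0 to 3.0 points
- k = 6: 2.0 to 6.0 points
- k = 9: 3.0 to 9.0 points

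Worked example: 24 stayers average 70 and 6 leavers would have averaged 45. The all-starter mean is (24 × 70 + 6 × 45)/30 = 1950/30 = 65, while the reported mean would be 70. With k = 0 the overstatement is 0.

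**The case against.** A reader might infer that every patient who stops early gives no score, so that the published satisfaction necessarily comes from stayers only. The article does not say this. Stopping the exercises is not the same as missing the week-8 assessment. That assessment is not restricted to completers, and the intention-to-treat commitment points towards assessing everyone who started. The Stage 4 sentence is also partly about compiling records, some gathered earlier, so it does not by itself rule out a TSUQ at exit. These objections stand. The point is therefore limited to patients who leave the research before week 8, for whom no score is described.

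A reader might also infer that feasibility is declared on satisfaction alone. It is not: delivery and adverse effects count too, session counts are automatic, and barriers are recorded daily. Heavy attrition would therefore show in the results, and a patient who left over a difficult application may already have that difficulty on record. This limits the damage but does not correct the TSUQ mean itself.

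Two further objections hold in part. The dropout rates and score gaps are assumed, and with no satisfaction threshold nobody can show that a given shift would reverse a conclusion. Exit procedures are also often left to a full protocol. Against this, the article does set out which measures are taken at which stage, and it gives the TSUQ one time only.

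**Conclusion.** The point holds as a risk. The TSUQ is named only at week 8, no score is planned for patients who have left the research by then, there is no baseline to work from, and satisfaction is one of the three elements of the feasibility conclusion. The direction is upward provided that leavers are on average less satisfied, which is plausible but not shown in the documents; patients who leave for unrelated reasons would add little bias.

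The size cannot be fixed. The widths of 6.8, 13.6 and 20.4 points need only the scale range, N = 30 and the assumed number missing. The overstatement of 1.0 to 9.0 points also rests on an assumed gap between stayers and leavers. If every starter answers at week 8, the concern disappears. No figure in the article is contradicted. This is a worthwhile, inexpensive improvement to a secondary outcome and does not invalidate the design.

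**What to change.** In Stage 4 of section 2.4, state that the TSUQ goes to everyone who started, at the time they stop the program or at week 8, whichever comes first. The email or messaging access already required for inclusion can carry it. State also that patients who stop the program but do not withdraw from the research are still assessed at week 8.

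In the feasibility statement in section 3, commit to reporting the number of TSUQ responders out of all starters and the session counts beside the responder mean. Add a worst-case bound as a sensitivity analysis, with each non-responder given the minimum of 17. This should remain a bound and not become the main result: treating every non-responder as dissatisfied has its own downward bias, and the article defines no cut-off for a favourable score.

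The cost is one existing questionnaire sent at a second possible time and a few lines in the report. Some patients who stop will not answer, those who withdraw altogether may decline, and the satisfaction result may look less favourable.

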### 2.5. Statistical Analysis

This research is a single center prospective controlled trial pre/post design. The results of the trial research will be presented as a summary of the outcome measures, together with the estimated effect size and precision. Statistical analysis will be performed according to the intention-to-treat principle. Patient characteristics will be summarized using frequencies and percentages for categorical factors, and using means and standard deviations for continuous measures in order to have as much information as possible available for exploration and analysis. The effect sizes will be calculated using Cohen’s d, so that the results can be compared to other studies. The outcome measures will be compared before and after the completion of the 8-week CTR program. All statistical analyses will be conducted using SPSS software. Statistical significance was set at *p* < 0.05.

## 3. Results

Enrollment began in February 2021. First study results will be reported in the middle of 2021. Recruitment is currently underway. The recruitment goal is 30 cardiac rehabilitation patients. Data collection is anticipated to be complete by July 2021.

If the results confirm beneficial effects in biochemical, cardiac function, quality of live, and functional capacity, the effectiveness of the intervention will be proven in patients with heart failure. The successful delivery of the intervention, the absence of significant adverse effects, and the user satisfaction will demonstrate the feasibility of these interventions in cardiac patients.

The results of this study will determine if a larger-scale intervention is feasible. Further, this pilot study will be the first to examine the effect of CTR intervention on patients in a cardiac rehabilitation setting in Melilla (Spain). The results of this study will provide differences compared to previous research: first of all, its implementation in the autonomous city of Melilla (located on the African continent with particular demographic characteristics); secondly the use of the innovative CTR platform based on the App Physiotec; thirdly, the collection of outcomes that combine clinical, self-reported and economic data and lastly, automated treatment adherence registry.

This study will add more evidence in support of the use of CTR program as an effective tool in new cardiac rehabilitation programs.

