### 2.2. Intervention

Participants are assigned to the cardiac telerehabilitation group to receive an initial assessment. The CTR group receives a personalized 8-week exercise program through a mHealth application that allows health professionals to generate videos, images, and parameters of each exercise, as well as send them by email, instant messaging, and follow up on patients. In this study, we use the Physiotec exercise prescription app as it allows us to create personalized CTR programs according to particular clinical case and follow their progress. The CTR program describes the exercises to be performed, the number of repetitions according to the level of training and the criteria for progression. The CTR program includes aerobic exercise at 60–85% of the maximum heart rate (HR) reached in the ergometry test. As patients are taking β-blocker drugs, they will never reach their maximum HR. Patients will be instructed in the use of the Modified Borg Scale to assess their level of fatigue while performing the CTR program. Exercises customized to each participant should be performed between values 4–6 on this scale (out of a maximum of 10).

The type of exercise can be continuous or intervallic (load or HR controlled):

Continuous Exercise: After an initial warm-up period of 5–10 min, the patient is brought into a phase where he or she remains at a HR or resistance previously determined by the intervention team.

Interval Exercise: After an initial warm-up period, an exercise is started which alternates load peaks with lower intensity ones.

All patient training sessions should end with a return to the initial baseline situation (relaxation phase) of similar duration to the warm-up phase 5–10 min.

Typical CTR training session: -Control of basal constants (by the patient): HR, blood pressure, weight, blood sugar…-Permanent monitoring during the whole CTR session (patient must understand and follow the modified Borg scale as well as to use activity bracelets, pulse meters, or other monitoring instruments)-Exercise session:
∘Initial warm-up: 5–10 min (follow-up the video exercises provided through the CTR tool).∘Aerobic training: 35–45 min (follow up the video exercises provided through the CTR tool)∘Return to calm, relaxation-cooling: 5–10 min (follow up of the video exercises provided through the CTR tool)∘Recording of incidents and patient feedback in the CTR tool. Patient/physiotherapist feedback

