The Charlson Comorbidity Index (CCI) will be included in the demographic, anamnesis and medical history data [33]. CCI is a system for evaluating life expectancy at ten years, depending on the age at which it is evaluated and the subject’s comorbidities. 

We will try to ensure that the sample data are similar at baseline and there are no significant differences in demographic, medical and other outcomes. The homogeneity of the sample will be analyzed and normality tests will be performed. An outline of the primary (4 dimensions) and secondary outcomes (3 dimensions) is shown at Table 2:

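### The study is labelled controlled and a good result is to count as proof of effectiveness, but the article describes one treated group and a before/after comparison only

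*Protocol article*

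**What the plan says.** The Abstract and the opening of Section 2 describe a prospective controlled trial at one center. Section 2.5 repeats the label: "This research is a single center prospective controlled trial pre/post design".

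The rest of the article describes one pathway:

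- Section 2.2 on assignment: "Participants are assigned to the cardiac telerehabilitation group to receive an initial assessment".
- Section 2.4 sets out four stages: a T0 assessment in cardiology, assessment in rehabilitation, treatment, and a T1 assessment. The treatment stage is "8 weeks CTR program with the supervision of the Physiotherapy Department and the CTR staff".
- Section 2.5 on the comparison: "The outcome measures will be compared before and after the completion of the 8-week CTR program". It also says "Statistical analysis will be performed according to the intention-to-treat principle".

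The end of Section 2.3.2 says the team will try to ensure that "the sample data are similar at baseline and there are no significant differences". The cost paragraph of the same section counts sessions in two groups, but no second group is defined anywhere in the article.

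Section 3 states what will be concluded. The condition is "If the results confirm beneficial effects in biochemical, cardiac function, quality of live, and functional capacity", and the consequence is "the effectiveness of the intervention will be proven in patients with heart failure". Section 2.1 and Section 4 leave adequate power and comparison groups to a later randomized trial.

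**The concern.** The label and the planned conclusion both go further than the described design allows. A controlled trial has a comparator, and this article describes none. Proof of effectiveness needs a contrast between what happened with CTR and what would have happened without it. A before/after comparison in one treated group measures the sum of the CTR effect and everything else that changes over 8 weeks.

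Efficacy is part of the main objective, and the Abstract names clinical guidelines as the place where the results should count. If the report follows Section 3 as written, any favorable change is credited to CTR, and readers may take the result for controlled evidence.

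**Working it through.** **Step 1. Is there a comparator?** The places in the article that bear on this, side by side:

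| Place | What it implies |
|---|---|
| Abstract, Section 2 opening, Section 2.5 | A control exists (label only) |
| Section 2.2 | Participants are assigned to CTR; no other assignment is described |
| Section 2.4, Stages 1 to 4 | One pathway: T0, 8 weeks of CTR, T1 |
| Section 2.5 | Comparison within patients, before versus after |
| Section 2.3.2, cost paragraph | Two groups, undefined |
| Section 4 | Comparison groups belong to a future trial |

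No control condition, allocation method or between-group analysis is stated. Even if the cost paragraph reflected a real second group, Section 2.5 gives no analysis that would use it. That every participant receives CTR is therefore a strong inference, not a statement of the article. Figure 1 is not available, but Section 2.4 describes its four stages in words.

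**Step 2. Could outcomes change without a CTR effect?** The article supplies four routes:

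- Table 1 enrolls patients after revascularized acute coronary syndrome. Recovery may still be under way; time since the event is not given.
- Section 2 leaves medication to the treating physician. Lipids, glucose, blood pressure and heart rate are primary outcomes in Table 2 and respond to drugs. Changes are to be documented and considered in the analysis, but without a comparator their effect cannot be separated reliably from that of CTR.
- Ergometry is done at T0 and again at T1, so familiarity with the test may contribute.
- SF-12, EQ-5D and DASI are self-reported, and no blinding is described.

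**Step 3. Illustration of size, for one outcome.** The article states no power, effect size or SD, so there is no figure of its own to reproduce.

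Inputs from the article: n = 30 (Sections 2.1 and 3) and a significance level of 0.05 (Section 2.5).

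Assumptions: two-sided test, paired t-test, complete data, zero CTR effect, and a favorable background drift of d = 0.2, 0.3 or 0.5 SD of the change score.

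Formula: the test statistic follows a noncentral t with 29 degrees of freedom and noncentrality d × √30, where √30 = 5.477. The critical value is 2.045. The probability of p<0.05 is P(T > 2.045) + P(T < −2.045).

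| Drift d | Noncentrality | P(p<0.05) |
|---|---|---|
| 0.2 | 0.2 × 5.477 = 1.095 | 0.185 |
| 0.3 | 0.3 × 5.477 = 1.643 | 0.355 |
| 0.5 | 0.5 × 5.477 = 2.739 | 0.754 |

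Nearly all of this is in the favorable direction (0.184, 0.355 and 0.754). With no drift, the corresponding figures are 0.05 in total and 0.025 in the favorable direction.

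**The case against.** **The article is open about being a pilot.** Sections 3 and 5 call it a pilot study, Section 2.1 defers adequate power to a later randomized trial, Section 3 says the results will show whether a larger intervention is feasible, and Section 2.5 promises effect sizes with precision. This stands, and it lowers the risk that the claim of proof is taken literally. It does not remove the claim; it contradicts it.

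**The claim of proof is conditional.** It is, but the only effects this plan can confirm are uncontrolled changes, so meeting the condition does not supply the missing comparison.

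**The probabilities are not this trial's error rate.** This stands. They describe one paired t-test on one outcome under assumed drift. Section 3 joins four domains with *and*. With one test per domain, all four required and independence, the figures would be 0.185⁴ ≈ 0.001, 0.355⁴ ≈ 0.016 and 0.754⁴ ≈ 0.32. Correlation between domains, or several measures per domain, would raise them. The article fixes no such rule and names no test.

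**Stronger readings that the article does not support.**

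- A reader might infer that intention-to-treat is itself an error here because it presupposes groups. In one arm it can mean analyzing all enrolled patients, so it needs clarifying only. The baseline sentence reads like a group comparison, but it is followed by a reference to the homogeneity of a single sample. It is unclear, not proof of an error.
- A reader might infer regression to the mean. Table 1 does not select patients on extreme values of any primary outcome, so this is not shown.
- A reader might infer that drug changes are ignored. Section 2 says they will be documented and considered.
- A reader might conclude flatly that no control group exists. The cost paragraph prevents that. What can be said is that none is described.

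**Conclusion.** The point holds as a mismatch between wording and design. The controlled label and the promise of proof are affirmative statements, not details that a condensed article leaves to a fuller document, and the design described in Sections 2.2, 2.4 and 2.5 does not support either. Following Section 3 as written would lead to a causal conclusion from an uncontrolled 8-week change. It needs correcting before results are reported.

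This rests on the text describing CTR as the only pathway and on no between-group analysis being stated. It does not depend on the probabilities, which only show that a modest background drift is enough to make a single before/after test significant much more often than 5%. The true size of any drift in these patients cannot be derived from the article.

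**What to change.** 1. In the Abstract, the opening of Section 2 and Section 2.5, replace *controlled trial* with *single-arm pre/post pilot study*. Sections 3 and 5 already say pilot study and need no change of label.
2. In Section 3, replace the statement that effectiveness will be proven with: *The mean 8-week change with its 95% CI will be described; it cannot be attributed to CTR without a comparator.*
3. Align the remaining efficacy wording with this: the aims in the Abstract and Section 1, the purpose of the sample size in Section 2.1, and the closing statements of Sections 3 and 5.
4. In Section 2.3.2, reconcile the cost paragraph's two groups and the baseline-similarity sentence with a one-group design. If a second group does exist, define it and state the between-group analysis instead.
5. In Section 2.5, state that intention-to-treat here means all enrolled patients, with T1 assessment sought from everyone regardless of sessions completed.

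The cost of the wording changes is a weaker claim. They require no extra patients or procedures, and the feasibility, adherence, safety and satisfaction aims are unaffected.
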